## Abstract

**Background:**

Breast cancer (BC) has particular characteristics in young women, with diagnosis at more advanced stages, a poorer prognosis and highly aggressive tumors. In NeoFit, we will use an activity tracker to identify and describe various digital profiles (heart rate, physical activity, and sleep patterns) in women below the age of 45 years on neoadjuvant chemotherapy for BC.

**Methods:**

NeoFit is a prospective, national, multicenter, single-arm open-label study. It will include 300 women below the age of 45 years treated with neoadjuvant chemotherapy for BC. Participants will be asked to wear a Withing Steel HR activity tracker round the clock for 12 months. The principal assessments will be performed at baseline, at the end of neoadjuvant chemotherapy and at 12 months. We will evaluate clinical parameters, such as toxicity and the efficacy of chemotherapy, together with quality of life, fatigue, and parameters relating to lifestyle and physical activity. The women will complete REDCap form questionnaires via a secure internet link.

**Discussion:**

In this study, the use of an activity tracker will enable us to visualize changes in the lifestyle of young women on neoadjuvant chemotherapy for BC, over the course of a one-year period. This exploratory study will provide crucial insight into the digital phenotypes of young BC patients on neoadjuvant chemotherapy and the relationship between these phenotypes and the toxicity and efficacy of treatment. This trial will pave the way for interventional studies involving sleep and physical activity interventions.

**Trial registration:**

Clinicaltrials.gov identifier: NCT05011721. Registration date: 18/08/2021.

Digital health involves the collection of large amounts of data with various devices, including activity trackers and mobile phones [28]. Activity trackers can be used to evaluate the number of steps taken each day, the distance covered, energy expenditure, heart rate and the quality and duration of sleep [29]. Digital phenotyping is defined as the use of data from personal digital devices, including smartphones in particular, for instantaneous quantification of the human phenotype at individual level in situ [30]. This approach provides longitudinal data concerning the everyday activities of patients in a continuous and ecological manner. The combination of digital phenotyping data, clinical data and patient-reported outcomes can be used to identify patterns of behavior in patients; these patterns can then be used as the basis for the optimization of patient care through precision, predictive and personalized medicine [30–34].

The single-arm NeoFit trial will be an interventional single-arm study with the primary objective of describing and identifying digital profiles (physical activity, sleep and heart rate) in young BC patients (below 45 years of age) on NAC. Its secondary objectives will be: 1) to compare the digital profiles of participants according to clinical and sociodemographic variables, 2) to analyze the effects of digital profiles on tumor response, immune infiltrate, treatment toxicity, surgical complications, quality of life and fatigue, 3) to develop models for predicting chemotherapy response, toxicity, fatigue and changes in quality of life during treatment.

## Methods

### Study design

The NeoFit study is a prospective, national, multicenter, single-arm, open-label study promoted by the Institut Curie (Paris, France) (Fig. 1). It will enroll 300 participants from two comprehensive cancer care centers in France, beginning in September 2021 during a one-year period.

**Fig. 1 Fig1:**
[figure not shown]
Participant flow chart for the NeoFit study, France (original flow chart)

This trial protocol conforms to the rules of the Declaration of Helsinki and was approved by the appropriate French ethics committee CPP Est I (ID RCB: 2021-A00268-33). The study database has been registered with the French national data protection authority (CNIL) (reference number: reference: 2,220,932 v 0). The study has been registered with http://www.clinicaltrials.gov (NCT number: NCT05011721, registration date: 18/08/2021). Written informed consent will be obtained from each participant.

### Study population

Participants meeting the following criteria will be included:1) Female,2) Between the ages of 18 and 45 years,3) Histologically confirmed BC, whatever its histological subtype (hormone receptor-positive (RH +), negative (RH-), with (*HER2* +) or without (*HER2-*) *HER2* overexpression, or triple-negative),4) NAC scheduled (up to the first day of neoadjuvant chemotherapy),5) Eastern Cooperative Oncology Group Performance status ≤ 2,6) Patient willing to participate for the entire duration of the study,7) Patient able to use a compatible smartphone or computer tablet to download the Withings Health Mate application (from iOS 10 and Android 5.0 or above),8) Patient with Internet access,9) Patient with valid health insurance,10) Patient able to read, write and understand French.

Patients will be considered ineligible if they meet any of the following criteria:1) Metastases present at BC diagnosis,2) Bilateral BC,3) Multifocal BC,4) History of cancer other than basal cell skin lesions and cervical dysplasia,5) Patient pregnant or breastfeeding,6) Impossibility of following the patient throughout the study for medical, social, family, geographic or psychological reasons,7) Patient incarcerated or under a supervision order.

### Recruitment

Eligible individuals will be invited to participate in the study at the time of NAC prescription. Investigators will check the eligibility criteria at the treatment initiation consultation, explaining the objectives of the study and the way in which it will be performed to the patient. After sufficient time for reflection, patients agreeing to participate will be asked to provide written informed consent.

### Setting up the activity tracker and explaining its use

Participants will be asked to wear a Withings Steel HR activity tracker (Withings, Issy-les-Moulineaux, France) round the clock, throughout the study period. The Withings Health Mate mobile phone application will first be downloaded onto a smartphone or tablet at baseline, and the clinical research assistant will instruct the participant in the use of the activity tracker. The participant will then be asked to accept and activate the sharing of data collected with the dedicated “NeoFit” study server at Institut Curie. Participants will be asked to synchronize the activity tracker regularly (ideally daily) via Bluetooth with the Withings Health Mate application, for automatic data transfer to the secure "NeoFit" space. A clinical research assistant will optimize follow-up during the course of the study, via a platform checking the downloading of data from the activity tracker determining whether questionnaires have been completed within the time limit.

### Evaluations

#### Modes of evaluation

All participants will attend three study consultations when attending the participating hospital center for their regular oncology consultation: an initial inclusion assessment (before the first day of neoadjuvant chemotherapy), a second assessment at the end of neoadjuvant chemotherapy, and a third assessment 12 months after inclusion (M12).

The activity tracker will collect information continuously via the Withings Health Mate application. At the end of the study, participants will be allowed to keep the activity tracker, with a transfer of the corresponding account to their own name.

Patient-reported outcomes will be evaluated by the answers provided on the questionnaires completed by all participants at the various time points. Patients will be able to assess the questionnaires directly via the REDCap Internet link of the NeoFit study, with a computer, smartphone or computer tablet. Each time that a new questionnaire requiring completion is posted online, the participants will be notified by e-mail and asked to complete it. If they encounter any problems completing the questionnaire, they will be able to contact the clinical research assistant to ask for help.

### Data collection

A complete data collection schedule is provided in Fig. 1. Missing data will be limited by the checking of the NeoFit professional dashboard by the clinical research assistant, to ensure that questionnaires are completed on time.

#### Clinical data

The clinical research assistant will collect clinical data from the electronic medical records of the participants. The data collected will include information already analyzed in the care context and concerning disease status, neoadjuvant treatment, surgical data for biopsy and tumor specimens, adjuvant treatment and cancer progression. Toxicity data will be collected throughout the study. Toxicity will be defined according to the National Cancer Institute’s Common Terminology Criteria for Adverse Events (NCI-CTCAE) v5.0, as the occurrence of severe toxicity of at least grade 3.

#### Lifestyle and sociodemographic data

Lifestyle and sociodemographic data will also be collected. We will record the socioprofessional status of participants, their alcohol and tobacco consumption, eating habits, and the distance between the patient’s home and the center (baseline and Month 12), via a non-validated self-administered questionnaire with an estimated completion time of 10 min.

#### Quality of life

Quality of life will be assessed with the European Organisation for Research and Treatment of Cancer Quality of Life Questionnaire (EORTC QLQ-C30) version 3, which was validated in 2000 [35]. This multidimensional questionnaire has been validated for use with cancer patients. It contains 30 items assessing five functional domains (physical, role, emotional, cognitive, and social), one overall quality-of-life domain, three symptom domains (pain, fatigue and nausea), and six individual items (dyspnea, insomnia, anorexia, diarrhea, constipation, and financial impact). Responses will be on a Likert scale ranging from "not at all" to "very much" and from "very poor" to "excellent" for the overall quality-of-life questions only. Scores will be standardized on a scale of 0 to 100. Higher scores will correspond to better functioning, a better overall quality of life and more symptoms. Mean completion time for this questionnaire has been estimated at 10 min.

#### Fatigue

Fatigue will be evaluated with the EORTC QLQ-FA12 version 1 module, which was validated for cancer-related fatigue in 2017 [36]. EORTC QLQ-FA12 contains 12 items assessing the physical, cognitive, and emotional domains of cancer-related fatigue. Participants will complete a four-point Likert-scale questionnaire, with responses ranging from "not at all" to "very much".

Scores will be standardized on a scale of 0 to 100, with higher scores suggesting a greater degree of fatigue. This questionnaire has an estimated completion time of five minutes.

#### Physical activity level

Physical activity level will be assessed with the Godin Leisure-Time Exercise Questionnaire (GSLTPAQ) version 1, validated for women with BC in 2015 [37, 38]. This validated self-administered questionnaire contains three main questions on the frequency of low-intensity (e.g., easy walking), moderate-intensity (e.g., brisk walking), and high-intensity (e.g., jogging) physical activity for at least 15 min in a typical week. The frequency of low-intensity exercise is then multiplied by three, that for moderate-intensity exercise is multiplied by five and that for high-intensity exercise is multiplied by nine and the various scores are then added together to obtain a total score. This total score identifies three categories of patients on the basis of physical activity levels: highly active (≥ 24 units), moderately active (14 to 23) and with low levels of activity (< 14 units). Completion time for this questionnaire has been estimated at three minutes.

#### Activity tracker

The activity tracker will record daily step counts, heart rate at 10-min or one-second (if the patient manually activates the workout mode) intervals, sleep parameters (total sleep duration, duration of the deep and light phases of sleep, number of awakenings and their duration, and sleep quality according to a score developed by Withings) and other physical activities recorded automatically or declared by the participant [39–44].

### Data security

#### REDCap eCRF

The REDCap database is accessible via a protected Internet interface. User authentication is based on the directory of Institut Curie employees. On connection to the database, users are asked to confirm their identity using the credentials of their institutional accounts.

REDCap has a strong authentication system, based on a "two-factor" authentication principle, with a validation code transmitted by SMS or e-mail at each connection. An audit trail system is used to trace any changes. Additions, deletions or modifications to the data are recorded, along with the identity of their authors.

The REDCap database is hosted on the institutional MySQL database cluster managed by the IT department. Mirror databases are housed on two separate servers: a master server and a backup server in case of incidents. The database is backed up daily and stored in dedicated spaces.

#### Withings Application Programming Interface (API)

A free guide to the use of the Withings API is available online (https://developer.withings.com). The data will be stored in a databased dedicated to the NeoFit project and will be accessible to only a few authorized members of the Data Office, for maintenance and automatic data feeding purposes, and to identified members of the project team for data analysis. Access to this database will be granted via dedicated user accounts.

The Withings storage database is fed by an automatic routine, with users unable to perform manual interventions. None of the data are deleted or modified. Data can only be added, by the retrieval, at a predetermined frequency, of new measurements from the activity tracker. The Withings storage database is hosted on a dedicated instance within the data infrastructure, a virtualized infrastructure distributed over 12 physical servers. It is therefore resilient to failure and is backed up daily.

### Statistical analysis

#### Sample size

 As the main objective of the study is descriptive, there is no need to define a minimum number of subjects. For model validation, we will divide our population into two groups: i) a training sample (*n* = 150) and ii) a validation sample (*n* = 100). The accuracy of the model for 150 subjects will therefore be about 8%.$$CI=2\times \surd \frac{p\times q}{n}$$

We hypothesize that 10% of the participants may be lost to follow-up. In the context of this study, that would mean not completing the questionnaires despite reminders, or not wearing the activity trackers. The inclusion of 300 participants is therefore expected to result in the collection of at least 250 completed questionnaires and 250 activity tracker datasets.

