In terms of the development of algorithms and prediction models, we will:i) Compare the clinical data to a historical Institut Curie database containing data for patients receiving neoadjuvant treatment for BC collected between 2002 and 2011,ii) Compare the characteristics of our population with those of worldwide users of Withings Steel HR activity trackers of the same age and with a similar BMI. However, we will have no access to the medical histories of the other users,iii) Develop models for predicting treatment efficacy and toxicity. We will use the clinical data (personal information, pathological variables and treatment-related variables) and digital phenotype of the BC patient. Treatment toxicity will be evaluated with questionnaires based on the CTCAE criteria. Chemotherapy efficacy will be assessed by evaluating pathological complete response rates and determining the number of nodes sampled after NAC. We will train the model on 150 patients and validate it on the remaining 100 patients.iv) Develop models for predicting fatigue and changes in quality of life during treatment. We aim to develop a statistical model for detecting correlations between treatment-related variables (e.g. drugs taken, number of cycles and their dates) and periods of fatigue or deterioration of quality of life characterized by abnormal changes in physical activity. A training/validation strategy similar to that described in (iii) will be used.We will start by constructing the classification tool, which we will then validate before performing comparative studies based on the resulting classification.

Statistical analyses will be performed with R software.

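### The stated model precision of about 8% is for the 150 training patients; for the 100 validation patients the same formula gives about 10 percentage points

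*Protocol article*

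**What the plan says.** The Sample size section of the protocol article first explains that the main objective is descriptive and so requires no minimum number of subjects. It then turns to validation of the prediction models and divides the population into "a training sample (*n* = 150) and ii) a validation sample (*n* = 100"). The next sentence gives the only precision figure in the document: "The accuracy of the model for 150 subjects will therefore be about 8" per cent. It is followed by the formula CI = 2 × √(p × q / n). No value of p is given, and no precision is given for n = 100.

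The Statistical methods section, item (iii) on models for treatment efficacy and toxicity, confirms the role of each sample: "We will train the model on 150 patients and validate it on the remaining 100 patients". Item (iv), on fatigue and quality of life, adopts a similar training and validation strategy.

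On attrition, the Sample size section says "We hypothesize that 10% of the participants may be lost to follow-up", and concludes: "The inclusion of 300 participants is therefore expected to result in the collection of at least 250 completed questionnaires and 250 activity tracker datasets".

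**The concern.** A binomial interval for the accuracy of a prediction model describes the sample in which accuracy is assessed. The plan holds out 100 patients for that purpose. Accuracy measured in the 150 patients used to build the model tends to be optimistic, which is the reason for having a validation sample. An interval based on n = 150 therefore describes a quantity that the plan does not treat as its validated result.

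The text introduces the split as serving model validation and presents the 8% as a consequence of it. A reader will naturally take 8% as the precision with which the validated models will be known. That precision is poorer, and the document does not state it. At stake is a correct account of what the third secondary objective (models for response, toxicity, fatigue and quality of life) can deliver.

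**Working it through.** **Inputs, all from the protocol article**

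- Training sample 150, validation sample 100 (Sample size; roles confirmed in Statistical methods, item iii).
- Formula 2 × √(p × q / n), with q = 1 − p (Sample size).
- Stated result: about 8% at n = 150 (Sample size).
- 300 enrolled, 10% loss, at least 250 datasets expected (Sample size).
- p is not stated. I take p = 0.5 as the worst case and show 0.3 to 0.6 as a range.

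**Step 1: reproduce the plan's figure.** At n = 150 and p = 0.5, 2 × √(0.25/150) = 0.0816, or 8.2 points. At p = 0.4 or 0.6, 2 × √(0.24/150) = 0.0800. The stated figure reproduces, as a half-width. The full width at p = 0.5 would be 2 × 8.16 = 16.3 points.

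**Step 2: apply the same formula to the validation sample.**

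| p | n = 150 (training) | n = 100 (validation) |
|---|---|---|
| 0.3 | 7.5 points | 9.2 points |
| 0.4 or 0.6 | 8.0 points | 9.8 points |
| 0.5 | 8.2 points | 10.0 points |

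For example, 2 × √(0.25/100) = 0.100. With a multiplier of 1.96 in place of 2, the value at p = 0.5 is 9.8 points.

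**Step 3: a check that does not need p.** For any fixed p the half-width varies as 1/√n. Taking the stated 8% at face value, 8 × √(150/100) = 8 × 1.225 = 9.8 points at n = 100.

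**Step 4: attrition, as a side note.** 300 × 0.90 = 270 patients, 20 more than the 250 in the split. If all 20 were added to validation, n = 120 and 2 × √(0.25/120) = 0.0913, or 9.1 points. That is still wider than the 8.2 points at n = 150.

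**The case against.** The strongest reply is that nothing has been miscalculated. The text says openly that the 8% is for 150 subjects, it never claims 8% for the other 100, and the difference is under two points. The plan also disclaims any need for a minimum number for its main objective, so no test, decision rule or primary analysis rests on the figure. All of this stands, and it limits the severity. It does not remove the point, because the figure is offered under the purpose of model validation and belongs to the sample that does not validate.

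It could also be said that 8 points can be reached at n = 100 if accuracy is higher: at p = 0.8, 2 × √(0.16/100) = 8.0. That is true, but the same p would give 6.5 points at n = 150, not the stated 8%. The value of p behind the plan's figure must lie near 0.4 to 0.6, and there n = 100 gives 9.8 to 10.0.

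A reader might infer more than the documents support:

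- **That the attrition figures contradict each other.** Ten per cent loss leaves 270, whereas 250 of 300 would be a 16.7% loss. But the plan expects 250 as a minimum, and 270 satisfies it. The inference is loose, but there is no shortfall. Where patients beyond 250 would go is a detail that a condensed article may leave to the full protocol.
- **That sensitivity will be far less precise than stated.** Subgroup half-widths could be computed from the 20–60% range for pathological complete response in the Background. But that is a literature range and not a planning assumption for this cohort, and the plan neither names sensitivity as a measure nor claims a precision for it.
- **That the label CI makes the figure wrong.** The formula gives a half-width and the number is used consistently as one. A clearer label helps, but no result changes.

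**Conclusion.** The point holds in a narrow form. The stated precision of about 8% is correct for n = 150 but is tied to the training sample. For accuracy in the 100 validation patients the plan's own formula gives a half-width of about 10 percentage points (10.0 at p = 0.5; 9.2 to 10.0 for p from 0.3 to 0.6; 9.8 by scaling the stated 8%). The published figure is thus too favourable by a factor of about 1.22, or just under two points.

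This rests on the plan's normal approximation with multiplier 2, on an assumed p (the document gives none), and on all 100 validation patients being evaluable for the outcome in question.

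Severity is minor to moderate. A reader might conclude that the sample size of 300 is undermined, but the documents do not support that: the plan does not derive 300 from the 8%, and the descriptive primary analysis by latent-class mixed models does not depend on it.

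**What to change.** In the Sample size section, give the precision for the sample in which accuracy is assessed. Suggested wording: with 100 validation patients, the 95% confidence interval for overall model accuracy will have a half-width of about 10 percentage points (2 × √(pq/n), assuming p = 0.5). If the n = 150 figure is kept, identify it as referring to the training sample and not to validated accuracy.

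Optionally, note that 10% loss from 300 would leave 270, that 250 is a conservative minimum, and how any patients above 250 would be allocated. If they all went to validation, the half-width would be about 9.1 points.

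The cost is a change of wording and a slightly less favourable published figure. No extra patients and no change to the design or analysis are needed.
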